### Effect measurement

The outcomes measured across implementation strategies and BHF intervention are described in Table 1. At the community level, the outcome associated with the fund and contract dissemination strategy is BHF program adoption, defined as (1) an objective count of communities responding to call for LOI and full application and (2) an objective count of communities responding to RFA and contracted to implement BHF. In addition, the BHF Online Training Resources and Program Package strategy targets outcomes of adoption, measured as an objective count of numbers of BHF cohorts initiated, and implementation, operationalized as community facilitator competence using the knowledge check score obtained from the BHF online training resource and direct observation of implementation fidelity (i.e., adherence to protocol, engagement, and dose [i.e., the number and duration of sessions conducted per cohort]). Finally, the LC implementation strategy involves outcomes of (1) reach, measured as the number, proportion, and representativeness of eligible family screened; (2) adoption, measured as an objective count of BHF cohorts initiated; (3) implementation fidelity, measured using the fidelity checklist via direct observation conducted by the trained research staff; and (4) sustainability, operationalized as an objective count of BHF cohort continued following the completion of LC sessions.

At the individual level, the effectiveness outcome will be assessed using a matched cohort design to determine changes in BMI *z*-scores from baseline to 6 and 12 months among BHF intervention participants across BHF-LC and BHF-PO conditions. We will apply an intention-to-treat approach when conducting the economic evaluation of the BHF intervention (effectiveness as the outcome measure).

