**Fund and contract** • Network weaving (recruitment of community) • Obtain formal commitment	**Adoption** -Objective count of communities & organizations responding to call for letter of intent -Objective count of communities & organizations responding RFA and contracted to implement BHF	-Draft the LOI -Draft the full application -Review the application materials -Meetings to discuss the applications & make a decision -Contact with the awardees -Obtaining the written memorandums	-Research team & CAB -Research team & CAB -Research team -Research team & CAB -Project coordinator -Project coordinator	Interested communities	Early	One-time for interested community	Duration of the meetings/telecommunications
**Learning Collaborative**^**b**^ • Network weaving (recruitment of BHF participants) • Consultee-centered training • Sustainability action planning	**Reach** -Number, proportion, & representativeness of eligible family screened -Representativeness of participating low-income families	-Document screening & engagement of low-income families -Create learning session materials that focus on identifying recruitment sources and channels to improve reach—with an emphasis on schools and clinics. -Delivery learning sessions that provide opportunities for community implementation teams to action plan recruitment procedures -Provide individual/group consultation on recruitment methods and outcomes -Follow up on action plans and outcomes using lighting report protocol -Provide action period consultation and reporting opportunities	-Research team -Research team -Research team -Research team -Research team -Research team	BHF-LC	Early-mid	Frequency of the sessions focusing on reach	Duration of the sessions
	**Adoption** -Objective count of the number of BHF cohorts initiated	-Create learning session materials -Delivery learning sessions -Provide individual/group consultation -Conduct knowledge/fidelity checklist -Provide feedback at each learning session -Complete pragmatic evaluations	-Research team -Research team -Research team -Research team -Research team -Research team	BHF-LC	Mid-late	Frequency of the training sessions focusing on adoption	Duration of the sessions

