### Eligibility, recruitment, and allocation

#### Community level

Applying the community engagement approach, the research team and the BHF-CAB disseminated the RFA within and outside their organizations and networks (i.e., applying network weaving strategy) and documented that communities across all 93 counties received the RFA. Eight communities with broad geographic distribution responded to the RFA of which seven rural communities in Nebraska completed a full proposal and were selected as the participating communities for the HEI trial. We then ranked the seven applications in a descending order and allocated the odd-numbered rankings to the (BHF-LC) and the even-numbered rankings to the package-only (BHF-PO) condition [23]. This exercise resulted in four communities in the BHF-LC condition and three communities in the BHF-PO condition. All communities that implement the PWMI will have access to the BHF Online Training Resources and Program Package that includes all of the materials necessary to implement and evaluate the BHF intervention.

Communities assigned to the BHF-PO condition are required to complete a memorandum of agreement (i.e., obtaining formal commitment strategy) to report on the implementation of the PWMI and to use pragmatic evaluation strategies for reach and effectiveness outcomes and to provide de-identified program data for baseline, 6, and 12 months. These communities will also have technical support as needed related to package function, but no other facilitation. Communities allocated to the BHF-LC condition will participate in LC training lessons with additional embedded implementation support activities with a goal to (1) develop local strategies to screen and engage families through the BMI Reporter in schools or clinical screening and referral, (2) increase implementation fidelity, and (3) plan for sustainability.

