#### Individual level

Recruitment will be completed by selected communities through school BMI report cards, physician referral, local advertisements, and through word-of-mouth based on locally available resources and guided by the BHF Online Training Resources and Program Package. All materials are designed for local adaptation based on location, time of the session, clinical and school partners, and form of recruitment used. For BHF participation, families will be eligible if they have a 6- to 12-year-old child with a BMI percentile ranking at or above the 95th percentile. Children with major cognitive or physical impairments, parents or children with a contraindication for physical activity and families participating in a concurrent PWMI will be excluded. According to our previous studies [20–22], 8–12 families per cohort would be ideal with a minimum of 5 families and a maximum of 12 families in each cohort. The study goal is to enroll 12 families (*n*=30–48 individuals) per cohort and 2 cohorts per community. With a total of 7 communities recruited, the total PWMI intervention participants are approximately 420–672 parent-child dyads.

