##### Sensitivity analysis

Performing a sensitivity analysis is a critical component of an economic evaluation when the assumptions and parameter estimates applied in the analysis have uncertain precision. Two approaches will be employed in the proposed economic evaluation. The first approach is one-way deterministic sensitivity analysis (DSA) [35] for the cost analysis of D&I strategies and BHF program training, recruitment and delivery. We will conduct the DSA around key unit costs, cost components, and outcome measures (i.e., BMI *z*-score) to assess the impact of these changes/variations on the total costs and cost-effectiveness [36, 37]. We will use tornado diagrams to summarize the effects of varying key input parameters one at a time on the results of the ICER/ACER [38]. Parameters to be considered include but are not limited to the role and salary level of key personnel, intensity/number of BHF sessions, and changes in the lengths of attendance time for the session. The parameters will be sorted in descending order by their influence on the ICER/ACER. The longer bars indicate the most important parameters. The second approach is a nonparametric bootstrap simulation, and it will be used to construct the joint uncertainty (e.g., 95% confidence interval) for the incremental costs and incremental effects (i.e., BMI *z*-score reduction) between BHF-LC and BHF-PO conditions. In the bootstrap simulation, 2000 random samples of cost-effect pairs will be selected with replacement from the original trial dataset. Simulation results will be presented graphically using a scatter plot (i.e., the incremental cost-effectiveness plane [ICEP]) [39], where each dot represents the ICER of one iteration of the bootstrap simulation. In addition, we will conduct CEA of BHF intervention using parents’ weight loss outcomes at 6 and 12 months. Moreover, we will conduct scenario analyses under different settings and conditions to estimate replication costs to enhance decision-making for potential adopting communities [40, 41].

All analyses will be performed using Stata 16.0 (StataCorp LP, College Station, TX) or Microsoft Excel.

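### The LC versus PO comparison of BMI z-score pairs an undefined matched design with intention-to-treat and states no baseline adjustment, although case-mix may differ between arms

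*Protocol article*

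**What the plan says.** Under Effect measurement, the protocol article states that "the effectiveness outcome will be assessed using a matched cohort design", covering change in BMI z-score from baseline to 6 and 12 months across the two conditions. The next sentence reads "We will apply an intention-to-treat approach when conducting the economic evaluation of the BHF intervention", with effectiveness as the outcome. The unit, variables and ratio of the matching are not given.

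The Effectiveness row of Table 1 divides C_LC − C_PO by E_LC − E_PO. Every LC activity is included in the LC cost. Data analysis interprets the ratio as the cost of one further unit of BMI z-score reduction. For uncertainty, Sensitivity analysis says that "2000 random samples of cost-effect pairs will be selected with replacement from the original trial dataset". None of these sections mentions matching or baseline adjustment.

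On recruitment, Individual level says "Recruitment will be completed by selected communities through school BMI report cards, physician referral, local advertisements, and through word-of-mouth". Community level says that applications were ranked, with odd ranks going to LC and even ranks to PO, giving four and three communities. It lists as an LC goal to "develop local strategies to screen and engage families through the BMI Reporter in schools or clinical screening and referral". Table 2 adds, for the LC only, the action "Create learning session materials that focus on identifying recruitment sources and channels to improve reach" and the reach outcome "Representativeness of participating low-income families".

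**The concern.** Three features make baseline differences between arms plausible: allocation was not random, families are recruited after allocation by communities that know their condition, and one arm is given extra help to change its recruitment channels and to reach low-income families. Child size is bounded only from below, at the 95th BMI percentile, so baseline severity has room to vary.

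The matched design is the only device the article names that could deal with this, and it is left open. A reader cannot tell which families enter E_LC − E_PO, or whether the bootstrap uses the same families. At stake is the meaning of the Effectiveness ICER: its denominator could partly reflect who enrolled rather than how comparable children fared, or the effect could come from a subset of families while the cost comes from all of them.

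**Working it through.** **The plan's own figure.** Individual level gives a goal of 12 families (30–48 individuals) per cohort, 2 cohorts per community and 7 communities.

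- 30 × 2 × 7 = 420 and 48 × 2 × 7 = 672, which reproduces the stated total as a count of individuals.
- Counted as families, the total is 12 × 2 × 7 = 168. The article labels 420–672 as dyads; that is a separate matter. The family count is used below.

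**Reading 1: matching families between arms.** LC families = 4 communities × 2 cohorts × f, and PO families = 3 × 2 × f, with f the families per cohort. The article gives a minimum of 5, an ideal range of 8–12 and a goal of 12. Assume one-to-one matching without replacement. The number of pairs cannot exceed the PO count, so at least LC − PO families are dropped.

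| f | LC | PO | LC dropped, at least | Share of LC | Share of all |
|---|---|---|---|---|---|
| 5 | 40 | 30 | 10 | 25% | 14% |
| 8 | 64 | 48 | 16 | 25% | 14% |
| 12 | 96 | 72 | 24 | 25% | 14% |

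At the goal, 96 − 72 = 24, 24/96 = 25% and 24/168 = 14%. At most 144 of 168 families remain, even with perfect matches. If only 80% of PO families found a match (again an assumption), there would be 57 pairs, so 114 of 168 families (68%) remain. The LC costs in Table 1 do not shrink with the matched set.

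**Reading 2: pairing baseline with follow-up within a child.** Nothing is balanced between arms, and a child without follow-up forms no pair. E_LC − E_PO is then an unadjusted difference between the children who completed follow-up.

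**How large could a case-mix bias be?** The article gives no figures for this, so every input here is assumed and the results are illustrations only.

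- Bias = baseline gap × slope of change on baseline. A gap of 0.2–0.4 z and a slope of 0.1–0.3 give 0.1 × 0.2 = 0.02 to 0.3 × 0.4 = 0.12 z.
- Bias = difference in subgroup share × difference in mean change between subgroups. A share difference of 10–30 points and a change difference of 0.05–0.20 z give 0.10 × 0.05 = 0.005 to 0.30 × 0.20 = 0.06 z.

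These ranges show that the answer depends on the assumptions. They do not estimate the bias in this trial.

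**The case against.** A reader might infer that matching and intention-to-treat contradict each other, so that the plan must either discard families or confound case-mix with the LC effect. The article does not support that. Full matching and weighting keep every enrolled family. Intention-to-treat may mean only that families are analysed under their community's allocated condition whatever their attendance, which matching does not by itself breach. Matched cohort may also just mean the same children followed over time.

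A reader might also infer that the arms are certain to differ. That goes too far. Both arms recruit through school and physician channels, and the package trains both on referral routes. The LC adds emphasis, and nothing says that it shifts child age or severity.

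The bootstrap wording is ordinary and compatible with repeating a matching step in each draw. Matching details may sit in the overarching trial's publications, to which the article refers, so their absence here is not in itself a fault. Effectiveness is a secondary aim of a pilot.

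There is also a fair point against heavy adjustment. If the LC changes the income mix or referral source of families, adjusting for these removes part of the LC's own effect while its recruitment cost stays in the numerator.

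All of this stands, and it limits the claim. It does not settle which families and which contrast form the ICER denominator: the article attaches two labels to one estimate and bootstraps it without saying how they fit together.

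**Conclusion.** The point holds in a limited form. The article fixes the effectiveness comparison poorly: an undefined matched design stands beside intention-to-treat, and the ICER and bootstrap then use E_LC − E_PO with no stated baseline adjustment, in a setting where case-mix may differ between arms.

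The one firm number is conditional. Under one-to-one between-arm matching, at least 24 of 96 LC families (25%) would be lost at the enrolment goal. The direction and size of any case-mix bias are unknown. No definite contradiction is shown. This is a worthwhile and inexpensive improvement to a secondary-aim analysis, which is also the outcome that the bootstrap is planned for.

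**What to change.** - Under Effect measurement, make the main effectiveness estimate a comparison of all enrolled families by allocated condition. Adjust the LC minus PO difference in BMI z-score at 6 and 12 months for baseline BMI z-score, child age and sex.
- Use that adjusted difference as E_LC − E_PO in the Effectiveness row of Table 1, and re-estimate it in each bootstrap draw under Sensitivity analysis.
- Report the raw difference alongside, so that readers can see how far the result depends on who enrolled.
- Adjust for income and referral source only as a sensitivity analysis, since the LC may itself change them.
- If matching is kept, use a form that retains all families, or restrict costs to the same matched set.

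The cost is a change of wording and a little analysis work, because baseline BMI z-score is already collected. Adjustment cannot remove unmeasured differences, and with 7 communities the covariate list must stay short.

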### Cost measurement

#### Labor costs

##### Dissemination and implementation strategies

The cost estimation of D&I strategies is guidied by the activity-based costing and Proctor framework, which is similar to the modified time-driven activity-based costing (TDABC) proposed by Cidav and colleagues [30]. We further extend the activity-based costing approach of implementation strategies to include opportunity costs, which are often overlooked and are key elements when considering the perspective of small-scale stakeholders [29], incurred by individuals (in our case, community facilitators) who are the target of D&I strategies. As the costs of D&I strategies are typically labeled as either labor (from performing the implementation activities) or non-labor costs (derived from the invoice or administrative data), the labor costs in a D&I strategy will be calculated by multiplying the hourly wages of personnel (*actor*) who conduct activities (*action*) associated with a D&I strategy with the amount of times and frequencies (*dose* and *temporality*) spent on activities plus the opportunity costs incurred by the strategy recipients (*action target*) (Table 2). The costs per D&I strategy will be calcuated as: $${C}_i={S}_i+\sum_{j=1}^m{X}_{ij}$$, where *C*_*i*_ = costs per discrete D&I strategy *i*; *X*_ij_=costs associated with activity *j* assigned to a D&I strategy *i*; *j* = activity *j* associated with a D&I strategy *i*; *j* = 1, 2, 3, …, *m*; and *i* =1,2,3,...; and *S*_*i*_ = amount of non-labor costs assigned to implementation strategy *i*. We will use the national hourly wage rate, corresponding to the position identified, of each community facilitator, CAB members, and research team members for estimates of labor costs.

Table 2 details the specification of each D&I strategy used in the HEI trial and the application of the specification for estimates of labor costs. For example, categorized by implementation activities, the actor in the fund and contract dissemination strategy includes research team members, CAB members, and a project coordinator. The hourly wage rate of each personnel involved in a specific activity can be easily derived from the the US Bureau of Labor Statistics [31]. The activities involved in this strategy including drafting the LOI and the full applications to be distributed to interested communities that may respond to the RFA, and reviewing the application materials, meetings to discuss the application and make a decision, and contacting the awardees. To obtain the total cost for each implementation activity, we will multiply the total time spent on each activity by each research team and CAB member and community facilitator by their corresponding hourly wage rate. Similar exercises will be applied to all other activities. The total labor cost of a discrete D&I strategy will be derived by summing up the total cost of each implementation activity associated with that discrete strategy. Similarly, we will calculate the total labor cost of the LC strategy and the BHF Online Training Resources and Program Package by summing up the costs associated with each activity specified (Table 2), applying the similar steps stated above.

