### Building Health Families Action Learning Collaborative (BHF-LC) to improve implementation quality

The BHF-LC represents the primary independent variable for the HEI trial whereby 2 to 4 communities receive only the BHF Online Training Resources and Program Package (package only, BHF-PO) and 2 to 4 communities will receive the package and participate in a LC (BHF-LC). The intent of a LC is to bring together community teams with members from different organizations and professional roles (e.g., staff, supervisors, senior leaders) to work together to learn BHF and sustain its use over time. Activities used in the LC model include pre-work activities to build capacity, in-person trainings, and implementation periods between trainings that involve ongoing consultation and quality improvement strategies [6]. Specifically, the BHF-LC includes collaborative learning sessions followed by action periods over a 2-year implementation period. The learning session topics align with the timing of BHF program activities with an early focus on reach and recruitment, followed by a focus on implementation quality, followed by a focus on maintenance of community program implementation. Consultee-centered training [27] is embedded within learning sessions to improve facilitator implementation capacity. This includes instruction on core content, review of BHF implementation data, facilitator reflection on implementation processes, goal setting and feedback relative to implementation outcomes, and group-based problem-solving to improve reach, implementation fidelity, and sustainability. Finally, sustainability action planning will be included in the BHF-LC and focus on strategies to embed program implementation within organization workflows and job responsibilities. The sustainability action planning will also include engaging local payers and public health organizations to explore opportunities for ongoing funding and reimbursement for implementation.

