### Overview of economic evaluation

This protocol has been reported in line with the Consolidated Health Economic Evaluation Reporting Standards (CHEERS) checklist [28] (see Supplementary File 1: CHEERS Checklist).

The economic evaluation of the HEI trial is two-fold. First is to conduct a cost and cost-effectiveness analysis of the fund and contract dissemination strategy for the BHF adoption, the BHF Online Training Resources and Program Package relative to BHF adoption and implementation, and the BHF-LC implementation strategy for promoting BHF adoption, implementation fidelity, and sustainability for the duration of the trial (12 months). The second is to conduct a cost and cost-effectiveness analysis of the BHF intervention. The CEA will be conducted from an implementing community [29] and limited societal perspective (i.e., including only productivity loss of participants due to the participation in the BHF program). The perspective of implementing community would include costs of time spent on planning, training, recruitment, delivering, and post-session follow-up, resources used, communication with the research team and BHF participants, and opportunity costs of community facilitators. Moreover, we will include the time and costs of the research team for providing training, facilitation, and technical assistance. Costs associated with research administration, data collection, and trial outcome assessment will be excluded. All costs will be categorized as labor and non-labor costs (e.g., space, supplies, or information technology) and expressed as US $2022. The unit of analysis for the economic evaluation is the 7 communities consisting of approximately 21–28 community facilitators who will be provided with BHF Online Training Resources and Program Package with or without a LC implementation strategy to implement and deliver the BHF intervention. The time horizon of the within-trial CEA will be across a 15-month period of time (first 3 months for preparation, and later 12 months for BHF intervention), to incorporate sufficient time to complete the whole implementation process of one BHF cohort, initiating from preparation, training, recruitment, and program delivery to post-intervention follow-up. This differs from the primary clinical effectiveness time horizon of 6 months. Costs and benefits will not be discounted due to a short duration.

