##### Data collection

To track all the activities associated with a D&I strategy and BHF program online training, recruitment and delivery, we use a publicly available time-tracking tool (i.e., Clockify), which is accessible through the website or smartphone app, to monitor the activities logging in by the community facilitators or the research team. To mitigate the potential respondent burden, we pre-populate the identified implementation activities associated with each D&I strategy proposed in the trial on the Clockify platform. Community facilitators in both conditions will be asked to record their BHF associated activities if any (typically the day before and the day of the BHF sessions) using either the web- or mobile-based Clockify app. They will receive weekly reminders for weekly implementation activity tracking, regardless of their group assignment, through an automated system email sent out during the weekend. In addition, the project coordinator will engage with the communities for reminders via emails, text messages, or phone calls if any given data was not logged in the system. We will supplement the cost data collection with meeting attendance sheets and minutes (for the research team and CAB members) and a BHF session check-in sheet (for participants).

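### On the community side only facilitators' time is recorded and priced, so LC-session time of supervisors and senior leaders is left out of the LC's cost

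*Protocol article*

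**What the plan says.** **Who the LC is for.** The section on the BHF Action Learning Collaborative gives its intent as to "bring together community teams with members from different organizations and professional roles (e.g., staff, supervisors, senior leaders"). Table 2 likewise describes the learning sessions as serving community implementation teams.

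**Whose time is costed.** Under Labor costs, the subsection on dissemination and implementation strategies extends activity-based costing to opportunity costs "incurred by individuals (in our case, community facilitators) who are the target of D&I strategies". It applies national hourly wages "of each community facilitator, CAB members, and research team members for estimates of labor costs". The worked example in that subsection multiplies the "total time spent on each activity by each research team and CAB member and community facilitator by their corresponding hourly wage rate" and is then carried over to all other activities. The perspective in the Overview of economic evaluation lists "communication with the research team and BHF participants, and opportunity costs of community facilitators".

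**Whose time is recorded.** Under Data collection, the time-tracking tool is used "to monitor the activities logging in by the community facilitators or the research team". It is supplemented by "meeting attendance sheets and minutes (for the research team and CAB members") and a check-in sheet for program participants. The exit interviews mentioned under Non-labor costs are with facilitators.

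**The general rule.** The same labor-cost subsection says that the opportunity cost of the strategy's recipients is added, and identifies recipients with the action target column of Table 2. For the LC that column reads BHF-LC, with no restriction by role.

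**The concern.** The people whom the LC brings together are a wider group than the community members whose time is recorded and priced. If supervisors and senior leaders attend learning sessions as intended, their hours are a cost to the implementing community, which is the stated perspective. No instrument named in the article records those hours and no wage is listed for them.

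The omission does not fall equally on the two conditions. LC sessions take place only in BHF-LC communities; the package-only communities receive technical support and no other facilitation. Table 1 charges LC sessions to C_LC alone, so time left out of them lowers the cost of one arm. The article itself calls recipients' opportunity cost a key and often overlooked element, and its Discussion criticizes an earlier costing method for leaving it out.

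**Working it through.** **1. The plan's head count.** The Overview gives 21–28 facilitators in 7 communities: 21 / 7 = 3 and 28 / 7 = 4 per community. The section on the packaged blueprint names training for a program facilitator and for three content areas, which is four roles, and 4 × 7 = 28 reproduces the upper figure. The stated count is therefore consistent with delivery staff alone. The four LC communities have 4 × 3 = 12 to 4 × 4 = 16 costed facilitators.

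**2. Coverage, side by side.**

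| LC attendee | Wage listed | Time source named |
|---|---|---|
| Research team | yes | time tracker, attendance sheets, minutes |
| CAB members | yes | attendance sheets, minutes |
| Community facilitators | yes | time tracker, exit interview |
| Other team members (supervisors, senior leaders) | no | none |

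**3. Where the omission enters Table 1.**
- Reach, Effectiveness and Adoption (cohorts initiated) use (C_LC − C_PO)/(E_LC − E_PO), with LC sessions or all LC activities in C_LC only.
- Implementation (fidelity) and Maintenance use C_LC/(E_LC − E_PO), with the package-only cost given as none. Here LC cost is the whole numerator.
- Adoption (fund and contract) and Implementation (package) use C_all/E_all and contain no LC session cost, so they are unaffected.

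**4. Direction.** If δ > 0 is the omitted cost, the numerator is too small by δ in the five LC rows. With E_LC − E_PO > 0 each ratio is too low by δ/(E_LC − E_PO). With a zero or negative effect the ratio cannot be read this way, but the incremental cost is still too small by δ.

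**5. Size, illustrative only.** The documents give no LC attendance, hours per attendee or wages. Let f be the costed facilitators per community (3 or 4, from step 1), k the uncosted team members per community (assumed 1 to 3) and w their wage relative to a facilitator's (assumed 1 to 2), with equal session hours.

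Share of LC recipient time cost missed = k·w / (f + k·w)

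| f | k | w | share missed |
|---|---|---|---|
| 4 | 1 | 1.0 | 1/5 = 0.20 |
| 3 | 3 | 1.0 | 3/6 = 0.50 |
| 4 | 1 | 1.5 | 1.5/5.5 = 0.27 |
| 4 | 2 | 1.5 | 3/7 = 0.43 |
| 3 | 3 | 2.0 | 6/9 = 0.67 |

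These are shares of recipient time cost. LC cost also holds research team and CAB time. Moving from one to the other needs a further assumption: if recipient time were 25% to 75% of true LC cost, LC cost would be understated by 0.20 × 0.25 = 5% up to 0.67 × 0.75 = 50%. A range that wide shows only that the documents do not settle the size.

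**The case against.** **The general rule is wider than the parenthesis.** Recipients are equated with the action target, and Table 2 does not limit that by role, so the intended costing may cover the whole team. This stands as a possible reading. But the parenthesis, the perspective, the wage list, the worked example and the time log all name facilitators as the only costed community members. If the whole team was meant, the passages still need reconciling, and no recording instrument is named for the rest of the team.

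**Facilitator is not defined as delivery staff only.** The four roles are audiences for training modules, not a head count, and the lower figure of 3 does not match four roles. That is fair: step 1 shows consistency and is not proof.

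**Other sources may fill the gap.** The limitations section adds field notes, exit interviews and the research team's own activity log. Since the research team delivers the sessions, that log may well show when they took place and for how long. These sources are offered, however, as a remedy for irregular logging by facilitators; nothing says that they count other attendees by role.

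**Leaders' time may arise in both arms.** The call to all applicant communities asked for decision makers as well as implementers. Their time outside LC sessions may therefore go uncosted in package-only communities too. This limits what can be said about net leader time, but not about LC-session time, which only one arm has.

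**A condensed article leaves forms to the full protocol.** That would excuse silence on attendance-sheet fields. Here the article states positively whose time counts.

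Three stronger readings are tempting and not supported. A reader might infer that only facilitators' time is priced at all; research team and CAB time is also priced. A reader might infer that payers attend the sessions and go uncosted; the article says only that sustainability planning will engage them. And a reader might take the list of roles as an attendance record; it states intent and gives examples.

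**Conclusion.** The concern holds in this form. The costing rules record and price a narrower community-side group than the LC is designed to bring together, and they conflict with the plan's own general rule for recipients. Followed as written, LC-session time of non-facilitator team members is missing from C_LC. The LC's incremental cost is understated, provided such members attend, and the LC-versus-package-only ratios are too favorable if the LC effect is positive.

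The direction of the cost error does not depend on the assumed figures; the size does. The range of 20% to 67% rests on assumed attendance, equal hours and assumed wage ratios. It describes recipient time cost, and a reader should not take it as the bias in C_LC or in any ratio.

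**What to change.** Define LC recipients as every community team member who attends a learning session, consultation or sustainability activity. Extend the attendance sheets to them, with role and hours. Price the time at the national wage for the role, and add it to C_LC in the LC rows of Table 1 and in the Effectiveness row. Treat any equivalent meeting in package-only communities the same way. Bring the perspective statement, the parenthesis on recipients, the wage list and the data-collection paragraph into line with that definition.

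If these hours cannot be recorded, state the exclusion and vary the number of attendees, hours and wage in the one-way sensitivity analysis already planned.

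The cost is slight: a few wording changes and some extra entries on sheets already kept. The LC ratios may come out somewhat less favorable.
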